## Abstract

**Background:**

Due to the COVID-19 pandemic, it is more essential than ever to implement protective measures in primary care centers to ensure patients’ safety. This protocol describes a quasiexperimental study on the use of a mobile chat platform as a clinical consultation tool for adolescents and primary health care physicians.

**Objective:**

The purpose of the quasiexperimental study is to demonstrate that the use of mobile phones and messaging apps increases the number of health consultations. The study will be performed as part of the Health and School program in the Anoia region.

**Methods:**

The quasiexperimental study will compare the number of face-to-face consultations to the number of consultations conducted on XatJove Anoia, as part of the Health in Schools program in the Anoia region. The study will involve the use of a new communication platform (ie, XatJove Anoia) for health care professionals and adolescents, and data on the number of face-to-face consultations will be collected as part of the same program in another region. Data will be collected from secondary schools during the academic year 2020-2021. Statistical analyses will be performed on the data that users will enter in the registration form. These data will be collected by means of a questionnaire, which will be submitted once the questionnaire is closed. The questionnaire will consist of multiple-choice questions, which will allow numerical values to be assigned to various responses in order to carry out statistical analyses.

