According to a pilot study, cystitis and contraceptive problems are among the top 10 reasons why patients have used a web-based tool to conduct a consultation [8]. Although these conditions can be embarrassing and difficult to talk about, it is important that they are dealt with by health care professionals. If ignored, these conditions can lead to serious, unwanted, and costly complications (eg, a failure to use contraception can lead to unwanted pregnancies and sexually transmitted diseases) [9,10]. The fact that users have routinely reported these problems by means of digital health interventions, such as e-consulta (ie, an asynchronous teleconsulting service for primary care professionals and health service users that is connected to primary care electronic medical records), is a positive sign with regard to the greater use of health services for sensitive and serious conditions. As an anonymous digital health intervention, XatJove has the potential to address the inefficient costs resulting from the underutilization of health services for embarrassing and stigmatized disorders.

Due to the current climate of the health crisis caused by the COVID-19 pandemic [11] and the need to reduce the risk of infection, it makes more sense than ever to avoid face-to-face consultations with nursing staff in schools and primary care center visits by young people. It should be noted that this does not mean that there will be a reduction in the number of consultations for health-related issues and the number of school programs. On the contrary, the health crisis is expected to generate an increase in the need for emotional support for young people, and such support requires tools that allow for the quick use of technology (ie, technology that adolescents and primary care center professionals are familiar with and use regularly).

The main objective of this protocol is to describe a quasiexperimental study that shows that the use of mobile phones and messaging apps leads to an increase in the number of health consultations for adolescents aged between 12 and 16 years, as part of the Health and School program in the Anoia region. The study also seeks to evaluate the degree of satisfaction among XatJove users via an electronic survey.

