## Methods

### Study Design

A quasiexperimental study that compares the total number of face-to-face consultations and XatJove consultations will be conducted as part of the Health and School program in the Anoia region (ie, the intervention group) during the 2020-2021 academic year. Data on the number of face-to-face consultations will be collected from the same program in the Osona region (ie, the control group). Problems that affect adolescents and relate to mental health, emotional and sexual health, drug use, alcohol, and tobacco will be recorded. The study population will include adolescents aged between 12 and 16 years who attend secondary schools in the Anoia region. We will use a pragmatic sample of 100 XatJove consultations. The total number of visits (ie, face-to-face visits and XatJove visits) that relate to the Health and School program in the Anoia region during the 2020-2021 academic year will be recorded.

The following variables will be recorded: (1) universal variables, including gender and age; (2) dependent variables, including the total number of visits (ie, face-to-face visits and XatJove visits) that relate to the Health and School program; and (3) independent variables, including the topic of consultations (ie, consultations for sexual health, alcohol, drugs, eating disorders, bullying, domestic abuse, mental health, COVID-19, and other topics).

To learn more about the usefulness of XatJove, students will be asked to participate in a follow-up study that involves a focus group.

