## Discussion

This aim of the pilot quasiexperimental study is to investigate the use of a mobile phone health chat service for adolescents from secondary schools in Anoia and nursing professionals from primary care centers in the same region.

The various studies that we previously participated in have shown that the use of a web-based communication tool for patients and professionals reduces the number of face-to-face visits [12,13], which is a very positive aspect with regard to the COVID-19 pandemic. Furthermore, the results of the study and the long-term and short-term impacts of XatJove will be used to revise the Health and School program, which is offered by the Department of Health. In other words, XatJove is a tool that will serve in the review of existing protocols. Web-based visits and consultations are gaining in popularity in the new health care environment that has resulted from the COVID-19 pandemic.

Web-based consultations can help with avoiding self-diagnoses, as it is common for people to search for information on the internet, which is not always a reliable source. Current evidence points to the importance of innovating and improving the treatment processes offered by health and school programs. One of our study’s strengths is that the results will be obtained from usual clinical practices, without having to implement any considerable organizational or structural changes.

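### The abstract compares face-to-face with XatJove consultations, which does not measure the increase in total consultations that the study sets out to show

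*Protocol article*

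**What the plan says.** The abstract's Objective is to "demonstrate that the use of mobile phones and messaging apps increases the number of health consultations", and the end of the Introduction repeats this for adolescents aged 12 to 16 in Anoia.

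The abstract's Methods then give the comparison: "The quasiexperimental study will compare the number of face-to-face consultations to the number of consultations conducted on XatJove Anoia". The next sentence adds that "data on the number of face-to-face consultations will be collected as part of the same program in another region", without saying what those data will be compared with.

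In the main text, Study Design opens with "A quasiexperimental study that compares the total number of face-to-face consultations and XatJove consultations will be conducted" and places this in Anoia, the intervention group. It continues: "Data on the number of face-to-face consultations will be collected from the same program in the Osona region (ie, the control group". It lists as dependent variable the sum of both channels and says that this sum will be recorded: "The total number of visits (ie, face-to-face visits and XatJove visits) that relate to the Health and School program".

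Two passages bear on substitution between channels. The Introduction says that, in the pandemic, "it makes more sense than ever to avoid face-to-face consultations with nursing staff in schools". The Discussion reports from earlier studies that "the use of a web-based communication tool for patients and professionals reduces the number of face-to-face visits".

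**The concern.** A contrast between two channels and the sum of those channels are different endpoints. Only the sum, set against what would have happened without chat, bears on an increase. The contrast shows which channel was used.

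The difference matters here because the authors themselves expect some movement from face-to-face to chat. A fall in Anoia's face-to-face visits improves the channel contrast for XatJove and, other things equal, lowers the total. The same event would therefore count for the intervention on one measure and against it on the other. If the final report follows the abstract, its main comparison will not answer its own objective.

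**Working it through.** The protocol article gives no consultation counts, error rates or effect size, so there is no planned figure to reproduce. The check has two parts.

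**1. What each section fixes**

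| Section | Quantity | Measures a change in the total? |
|---|---|---|
| Abstract, Objective; Introduction | Number of consultations should rise | This is the target |
| Abstract, Methods, first sentence | Face-to-face against XatJove | No |
| Abstract, Methods, second sentence | Other region's face-to-face data collected | No contrast stated |
| Study Design, opening sentence | Face-to-face and XatJove; can be read as a sum or as one against the other | Unclear |
| Study Design, control group | Osona face-to-face data | Supplies a comparator; contrast not stated |
| Study Design, dependent variable | Face-to-face plus XatJove | Yes, if set against a comparator |
| Statistical Analysis | Means, medians, registration-form and questionnaire data | Does not settle it |

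If the abstract is instead read as Osona face-to-face against Anoia XatJove, it still leaves out Anoia's own face-to-face visits and so is not a comparison of totals.

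**2. Whether the two measures can disagree**

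Let X be XatJove consultations in Anoia, F the face-to-face visits that remain there, and T the total Anoia would have had without chat. The channel contrast is X/F. The change in the total is F + X - T. XatJove leads when X > F, that is, when X/(F + X) > 1/2. T does not appear in that condition.

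X = 100 is taken from the pragmatic sample in Study Design as a convenient value. All other counts are assumed.

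Pure substitution (F = T - X, so the total changes by 0):

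| T | F | X | X/F |
|---|---|---|---|
| 120 | 20 | 100 | 5.0 |
| 150 | 50 | 100 | 2.0 |
| 199 | 99 | 100 | 1.01 |
| 200 | 100 | 100 | 1.0 |
| 250 | 150 | 100 | 0.67 |
| 400 | 300 | 100 | 0.33 |

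The contrast runs from 5.0 to 0.33 while the total never changes.

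Pure addition (F = T):
- T = 200: the total is 300, a rise of 100/200 = 50%, with X/F = 0.5.
- T = 400: the total is 500, a rise of 100/400 = 25%, with X/F = 0.25.

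Falling total: T = 300, F = 100, X = 150. The total is 250 and 250/300 = 0.833, a fall of 17%. X/F = 150/100 = 1.5, and chat's share is 150/250 = 60%.

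The channel contrast can therefore favour XatJove when the total is flat or falling, and go against it when the total rises.

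**3. Why the combined count needs a denominator**

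Let N_A and N_O be the eligible students in Anoia and Osona, and F_O Osona's face-to-face count. The rate ratio is [(F + X)/N_A] / [F_O/N_O] = [(F + X)/F_O] × (N_O/N_A). The raw count ratio equals the rate ratio only if the two eligible populations are the same size. The document gives neither size.

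**The case against.** The strongest reply is that the main text already holds the right elements. Study Design names an intervention region and a control region, makes the sum of both channels the dependent variable, and says the sum will be recorded. The abstract also mentions data from another region. On this view the fault is loose wording in a summary. Much of that stands: a reader might infer that the study as designed cannot show an increase, and the document does not support so strong a reading. What remains is that no sentence sets the Anoia total against Osona, and the one comparison of counts stated without ambiguity is the wrong one. Leaving detail to an analysis plan does not answer this, because the problem is a statement that conflicts with the objective, not an omission.

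Two other strong readings also fail. A reader might infer that pure substitution always favours XatJove. It does so only when more than half of consultations move to chat, as the rows for T = 250 and T = 400 show. A reader might also infer that the protocol would count more XatJove than face-to-face consultations as success. No section states such a rule; the objective is framed as more consultations.

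Finally, straight after the sentence on avoiding face-to-face contact, the Introduction says that this does not imply fewer consultations and that need is expected to grow. The authors do separate channel shift from volume there, which makes it easier to do the same in the stated comparison.

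**Conclusion.** The point holds as an internal inconsistency. The abstract's comparison, and one reading of the design sentence in Study Design, conflict with the objective and with the listed dependent variable. The channel contrast carries no information on the change in the total: in the illustrations it favours XatJove 1.5 to 1 with a 17% fall, and goes against XatJove 1 to 4 with a 25% rise. These counts are assumed and show direction only; the size of any real discrepancy cannot be computed from the document. The algebra behind them needs no assumed counts.

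The repair rests on one further assumption, that Osona's consultation rate stands in for what Anoia's would have been without chat. The point is one that should be fixed. It decides what the study may conclude, but the data elements for the right contrast are largely planned already.

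**What to change.** In the abstract's Methods and in Study Design, state the same single primary comparison: combined Anoia consultations (face-to-face plus XatJove) against Osona face-to-face consultations over the same period, each expressed on a common denominator, for example per eligible enrolled student, and not as raw counts. Reword the opening sentence of Study Design so that it can be read only in this way. Keep the face-to-face and XatJove split within Anoia as a descriptive measure of displacement. Base any claim of an increase on the combined rate.

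The cost is wording in two places plus school enrolment figures for the two regions, which the article does not mention collecting. The drawback for the investigators is that high use of the app alone would not support a claim of increase.

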**Results:**

The study is projected to start at the beginning of November 2020 and finish in June 2021, which is when data analysis is expected to start.

**Conclusions:**

The results of the quasiexperimental study may assist in the development and planning of school health programs.

**Trial Registration:**

ClinicalTrials.gov NCT04562350; https://clinicaltrials.gov/ct2/show/NCT04562350.

**International Registered Report Identifier (IRRID):**

PRR1-10.2196/25062

This community-based outreach program requires intervention and cooperation from different professionals. One of the program’s main lines of activity is the open consultation service, in which a health care professional visits schools to facilitate primary care accessibility among adolescents and guarantee privacy, confidentiality, and proximity.

Patients—particularly adolescent patients—are often reluctant to seek counselling and health treatment for embarrassing or stigmatized conditions, which can result in the underutilization of primary care health services. In addition, searching for medical information on the internet (eg, searching via Google) is increasingly common. Primary care health services, which are often made for young people, include consultations for sexual and reproductive health problems [5] and mental health disorders [6]. Finding information on health-related issues can lead to serious problems; the underutilization of primary care services that provide information on certain issues and the untrustworthy nature of advice on the internet can subsequently lead to health complications that may require expensive and specialized medical interventions in the long run, which may result in increased care costs [4].

To avoid health complications and increased care costs, a tool that adolescents have easy, constant, and effective access to is required. Digital health interventions have been shown to minimize hesitancy in seeking health advice for stigmatized and embarrassing problems. The digital health innovations proposed by the company Abi Global Health (AGH) could provide a possible solution [7]. AGH has developed an asynchronous, mobile text-based communication platform that connects users to health care professionals. These professionals provide users with appropriate guidance to help them make informed decisions about their health. AGH operates in more than 10 countries and has a network of more than 300 health professionals. This preexisting tool will form the basis of XatJove Anoia (ie, YouthChat Anoia), which is a platform that attempts to provide resources for mobile communication and message exchanges between adolescents and primary care professionals. A quasiexperimental study on XatJove Anoia will take place in Anoia, which is a country in Central Catalonia.

According to a pilot study, cystitis and contraceptive problems are among the top 10 reasons why patients have used a web-based tool to conduct a consultation [8]. Although these conditions can be embarrassing and difficult to talk about, it is important that they are dealt with by health care professionals. If ignored, these conditions can lead to serious, unwanted, and costly complications (eg, a failure to use contraception can lead to unwanted pregnancies and sexually transmitted diseases) [9,10]. The fact that users have routinely reported these problems by means of digital health interventions, such as e-consulta (ie, an asynchronous teleconsulting service for primary care professionals and health service users that is connected to primary care electronic medical records), is a positive sign with regard to the greater use of health services for sensitive and serious conditions. As an anonymous digital health intervention, XatJove has the potential to address the inefficient costs resulting from the underutilization of health services for embarrassing and stigmatized disorders.

Due to the current climate of the health crisis caused by the COVID-19 pandemic [11] and the need to reduce the risk of infection, it makes more sense than ever to avoid face-to-face consultations with nursing staff in schools and primary care center visits by young people. It should be noted that this does not mean that there will be a reduction in the number of consultations for health-related issues and the number of school programs. On the contrary, the health crisis is expected to generate an increase in the need for emotional support for young people, and such support requires tools that allow for the quick use of technology (ie, technology that adolescents and primary care center professionals are familiar with and use regularly).

The main objective of this protocol is to describe a quasiexperimental study that shows that the use of mobile phones and messaging apps leads to an increase in the number of health consultations for adolescents aged between 12 and 16 years, as part of the Health and School program in the Anoia region. The study also seeks to evaluate the degree of satisfaction among XatJove users via an electronic survey.

Our main hypothesis is that the use of XatJove will improve the early detection of health problems, the accessibility of reliable information for young people, and communication among nursing professionals in primary care centers, in terms of issues related to drugs, diet, emotional health, and sexuality. We also believe that XatJove can help with the detection of child abuse cases.

## Methods

### Study Design

A quasiexperimental study that compares the total number of face-to-face consultations and XatJove consultations will be conducted as part of the Health and School program in the Anoia region (ie, the intervention group) during the 2020-2021 academic year. Data on the number of face-to-face consultations will be collected from the same program in the Osona region (ie, the control group). Problems that affect adolescents and relate to mental health, emotional and sexual health, drug use, alcohol, and tobacco will be recorded. The study population will include adolescents aged between 12 and 16 years who attend secondary schools in the Anoia region. We will use a pragmatic sample of 100 XatJove consultations. The total number of visits (ie, face-to-face visits and XatJove visits) that relate to the Health and School program in the Anoia region during the 2020-2021 academic year will be recorded.

The following variables will be recorded: (1) universal variables, including gender and age; (2) dependent variables, including the total number of visits (ie, face-to-face visits and XatJove visits) that relate to the Health and School program; and (3) independent variables, including the topic of consultations (ie, consultations for sexual health, alcohol, drugs, eating disorders, bullying, domestic abuse, mental health, COVID-19, and other topics).

To learn more about the usefulness of XatJove, students will be asked to participate in a follow-up study that involves a focus group.

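### Two channels are counted in Anoia and only one in Osona, so a shift from face-to-face to remote contact could appear as an increase in consultations

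*Protocol article*

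**What the plan says.** The aim (Protocol article, Introduction) is to show that mobile messaging "leads to an increase in the number of health consultations for adolescents aged between 12 and 16 years". Study Design defines what is recorded in the intervention region: "The total number of visits (ie, face-to-face visits and XatJove visits) that relate to the Health and School program in the Anoia region". For the control region it says: "Data on the number of face-to-face consultations will be collected from the same program in the Osona region (ie, the control group". The Abstract (Methods) has the same restriction: "data on the number of face-to-face consultations will be collected as part of the same program in another region".

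Three statements elsewhere bear on how contacts may move between channels in the study year:
- The Introduction argues that, because of COVID-19, "it makes more sense than ever to avoid face-to-face consultations with nursing staff in schools and primary care center visits by young people". It then adds: "It should be noted that this does not mean that there will be a reduction in the number of consultations for health-related issues".
- The Introduction describes a remote service that users already turn to for sensitive problems: "e-consulta (ie, an asynchronous teleconsulting service for primary care professionals and health service users". It is linked to the primary care electronic record. It is not part of the outcome in either region.
- The Discussion reports from previous studies that "the use of a web-based communication tool for patients and professionals reduces the number of face-to-face visits".

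Data Collection and Sources of Information takes visit totals from the primary care information system and XatJove queries from the platform's own database.

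**The concern.** The two regions are compared on different sets of channels. In Anoia a young person who would have been seen in person and uses XatJove instead is still counted. In Osona a young person who would have been seen in person and uses a remote service instead is not counted. Within Anoia, moving from e-consulta, which is uncounted, to XatJove, which is counted, would also register as a gain.

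The protocol's own premises are that in-person contact is better avoided and that consultations need not fall. Together they make some movement to remote contact plausible. If it happens in both regions, the unequal count favours the intervention on the main objective. A later analysis could not repair this, because the Osona remote contacts would not have been collected.

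**Working it through.** The only planned number is a pragmatic sample of 100 XatJove consultations. It comes without rates, effect size, error level or power, so there is no figure to reproduce. The check asks what the planned comparison would show if XatJove had no effect on the total.

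**Inputs from the protocol.** Anoia counts face-to-face plus XatJove, and Osona counts face-to-face only (Study Design). Another remote channel exists and is in neither count (Introduction).

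**Assumptions, because the protocol gives no figures.** Both regions have the same true number of consultations, M. In both, a share s moves from face-to-face to remote contact. Of Anoia's remote contacts, a share c goes through XatJove. The rest of Anoia's remote contacts and all of Osona's are uncounted.

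**Expected counts.**
- Anoia: M(1 − s) + M·s·c
- Osona: M(1 − s)
- Apparent ratio: (1 − s + s·c)/(1 − s)

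| s | c = 0 | c = 0.5 | c = 1 |
|---|---|---|---|
| 0 | 1.00 | 1.00 | 1.00 |
| 10% | 1.00 | 0.95/0.90 = 1.06 | 1/0.90 = 1.11 |
| 20% | 1.00 | 0.90/0.80 = 1.125 | 1/0.80 = 1.25 |
| 30% | 1.00 | 0.85/0.70 = 1.21 | 1/0.70 = 1.43 |
| 50% | 1.00 | 0.75/0.50 = 1.50 | 1/0.50 = 2.00 |

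The true ratio is 1.00 throughout. The last column is the upper case, in which every remote Anoia contact goes through XatJove.

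**Tied to the planned 100 XatJove consultations.** Suppose all 100 replace face-to-face visits and Osona moves the same number to uncounted remote contact (again c = 1). The apparent ratio is M/(M − 100):
- M = 200: 2.00
- M = 500: 1.25
- M = 1000: 1.11
- M = 2000: 1.05

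The protocol does not give M.

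**Chance of a false finding.** The article names no test, so this assumes a two-sided 5% test of the log rate ratio with Poisson counts a and b and standard error √(1/a + 1/b). In the upper case (c = 1):
- M = 200: 18% at s = 10% and 56% at s = 20%
- M = 500: 37% and 91%
- M = 1000: 63% and 99.7%

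For example, with M = 500 and s = 10%, a = 500 and b = 450. The log ratio is 0.105, the standard error 0.065 and the expected z 1.62. It exceeds 1.96 with probability about 37%.

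**After the fix.** If remote contacts are counted in both regions, each count is M(1 − s) + M·s = M. The expected ratio is 1.00 for every s and c, and the assumed test keeps its 5% level.

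**The case against.** The strongest reply is that the unequal channel list is the intervention itself. The outcome is limited to visits belonging to the Health and School program. The one consultation channel that the Introduction describes for that programme is a professional visiting the school. XatJove is the added channel, so on this reading every programme channel is counted in each region. If Osona visits are avoided and simply lost, an excess in Anoia is a real gain in access. This reply stands as a possibility, but the plan does not say that Osona has no remote programme contacts and collects nothing that would show it.

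The reply also rules out three stronger readings:
- **That Osona adolescents will in fact drop out of the control count.** A reader might infer this, but e-consulta appears only as background and is not tied to Osona, to this programme or to this age group. Telephone consultations are not mentioned at all. The protocol argues for avoiding in-person contact but does not forecast how much will be avoided.
- **That no shift of channel can be separated from more consultations.** Movement from face-to-face to XatJove inside Anoia nets out, because both are in the sum. The problem is confined to contacts that leave the count in Osona, or that enter it in Anoia from an uncounted remote channel.
- **That 1/(1 − s) is the size of the bias.** That is the ceiling. Anoia contacts that go to e-consulta are uncounted too, and at c = 0 the ratio is 1.00.

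**Conclusion.** The concern holds in conditional form. As written, the outcome is ascertained through two channels in one region and one channel in the other. If programme-type consultations in Osona move to uncounted remote contact while those in Anoia move to XatJove, an increase can appear with no true effect, and the planned data could not reveal it.

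The size cannot be fixed from the document. With equal demand and an equal shift in both regions, the apparent ratio runs from 1.00 (no shift, or no remote Anoia contact through XatJove) to 2.00 (half of contacts shift, all of Anoia's through XatJove). At a 20% shift it is 1.125 to 1.25 for c between 0.5 and 1. The false-positive rates also rest on an assumed test and assumed volumes, and apply to the upper case.

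The document does not support a claim that the result will be biased, or by how much. It does support the claim that the main comparison is open to this bias and has no safeguard against it.

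**What to change.** Define the primary count as all Health and School programme contacts (or contacts on the programme's topics) by 12- to 16-year-olds, through the same set of channels in both regions. It should include any remote contacts held in the primary care information system, plus XatJove in Anoia. Keep the count to the programme or its topics, so that it does not become a measure of all primary care use. Report face-to-face and remote counts separately by region. Keep face-to-face plus XatJove against face-to-face as a sensitivity analysis. If Osona has no remote programme contacts, state that and how it was established.

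The cost is a change of wording and a wider query. Visit totals already come from the primary care information system, and the protocol says that e-consulta is connected to the electronic record, so extraction looks feasible. The protocol does not confirm that such contacts can be identified by programme or topic. The main downside is that this coding may be less complete for remote contacts than for visits, so completeness should be reported by channel and region.
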